### Primary and secondary outcome measures

#### Primary outcome measure

The primary domain for improvement for both interventions in the trial is cancer-specific QoL. Cancer-specific QoL is measured by the QoL scale of the European Organisation for Research and Treatment of Cancer (EORTC) QLQ-C30. The EORTC QLQ-C30 has a validated Dutch-language version available [23].

#### Secondary outcome measures

Secondary outcome measures are perceived behavioural control, anxiety, patients' satisfaction with follow-up, generic health-related quality of life and societal costs. Perceived behavioural control is measured by the Dutch version of the Mastery Scale [24]. A question whether the patient is experiencing emotional support from partner (if applicable) is added. Anxiety is measured by the validated Dutch version of the State-Trait Anxiety Inventory (STAI) [25]. Patients' satisfaction with follow-up will be assessed using the validated Patient Satisfaction Questionnaire – NL (PSQ-NL) [26]. Generic health-related quality of life is measured by the EuroQol-5D (EQ-5D) [27].

Societal costs are determined by the hospital information systems and prospective cost-diaries. More details on the costs are provided in the economic evaluation section.

#### Time schedule

Patients complete questionnaires at baseline, and at 3, 6, 12 and 18 months intervals. Costs-diaries are filled out by the patients over a four week period, at the same time points. The questionnaires and cost-diaries are sent by mail. If not returned within 14 days, patients are contacted by the research assistant and are asked to continue participation.

### Statistical analyses

To evaluate differences in QoL outcome between the study arms, the data will be analysed using a multivariate linear regression model. In this model both the EGP factor and the telephone factor will be taken into account. In addition, variables such as age, hospital treatment, and experienced support of a partner, will be brought into the model. The procedure will be performed 4 times as QoL is assessed at 3, 6, 12 and 18 months. Differences in satisfaction with care, perceived behavioural control and anxiety will be analysed in the same way. Participation at group meetings will be analysed using logistic regression models. Differences in medical consumption will be evaluated using a multivariate linear regression model. Subgroup analysis will be performed to identify specific patient characteristics that could predict the optimal follow-up strategy for the individual patient. Data will be analysed according to the intention-to-treat principle.

The number of recurrences is expected to be very low with a follow-up of 18 months [28]. Statistical analysis of the difference in time-to-detection per group will therefore be limited to descriptive statistics.

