#### Sample size calculations

The primary outcome measure is cancer specific QoL at 12 months after randomisation, measured by the global health/QoL scale of the EORTC QLQ-C30. A baseline score of 64 with a standard deviation of 17 [19,20] is considered as a starting point. In an analysis of the clinical significance of changes in QoL, Osoba et al (1998) showed that patients judge a change between 5–10 to be small, between 10–20 to be moderate, and more than 20 to be large [21]. Consequently, we considered a change smaller than 5 points to be no change. To show that QoL of patients in arms 2 and 4 (telephone follow-up) is at least similar to patients in arm 1 and 3 (usual follow-up) with a power of 80% and a significance level of 0.05, the required number of patients per group is 80. With these 320 patients an improvement in QoL, by adding the EGP compared to no EGP, of 10 points with a power of 0.95 and a significance level smaller than 0.01 can be detected. A dropout rate of 10% is accounted for in these calculations.

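### The trial is sized to show that telephone follow-up is no worse by 5 points or more, but the stated analysis only looks for differences and is not tied to that limit

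*Protocol article*

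**What the plan says.** The Sample size calculations section of the protocol article names the global health/QoL scale of the QLQ-C30 at 12 months as primary. It starts from "A baseline score of 64 with a standard deviation of 17" and, citing published work on how patients judge changes in score, says "we considered a change smaller than 5 points to be no change". The telephone comparison pools over the educational group programme (EGP). Its aim is "To show that QoL of patients in arms 2 and 4 (telephone follow-up) is at least similar to patients in arm 1 and 3" (standard follow-up). The size derived for this aim is given as follows: "with a power of 80% and a significance level of 0.05, the required number of patients per group is 80". Dropout of 10% is included. The EGP has a separate target in the same paragraph: a 10-point improvement.

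The Statistical analyses section then gives a single QoL analysis: "To evaluate differences in QoL outcome between the study arms, the data will be analysed using a multivariate linear regression model". Both factors enter this model with covariates, and it is fitted separately at each of the four post-baseline assessments. The section adds: "Data will be analysed according to the intention-to-treat principle". It does not refer to the 5-point limit, to a confidence limit, or to a criterion for concluding that telephone follow-up is at least similar. The side of the 0.05 level is not given in either section.

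**The concern.** The two factors carry different kinds of hypothesis. For the EGP the question is whether QoL improves, and a test for a difference answers it. For telephone follow-up the question is whether QoL is not worse by an amount that matters. A test of zero difference does not answer that, because failing to reject zero is compatible with a loss of 5 points or more when the estimate is imprecise. Since the article describes one analysis for both, in the language of differences, nothing in it says how the telephone coefficient is to be judged against the limit that fixed the sample size.

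This is the primary outcome for one of the two interventions, and the conclusion would support replacing clinic visits by telephone contact. If the rule is settled only once the estimate is known, the choice between a difference test, a 90% interval and a 95% interval could decide the conclusion.

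**Working it through.** **Inputs** (all from Sample size calculations): limit 5 points, SD 17, power 80%, level 0.05, dropout 10%, 80 per arm. Four arms give 320, so each telephone level pools two arms: 160 v 160 randomised and 160 × 0.9 = 144 v 144 evaluable. True difference 0 is assumed for sizing.

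**1. Reproduce the stated sample size.** Per telephone level, n = 2(z_α + z_β)² × SD² / margin².

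- Non-inferiority, one-sided 0.05: 2 × (1.645 + 0.842)² × 17² / 5² = 142.9; / 0.9 = 158.8; / 2 = 79.4, i.e. 80 per arm. This matches.
- Non-inferiority at one-sided 0.025, or a two-sided 0.05 test to detect a 5-point difference: 2 × (1.960 + 0.842)² × 17² / 5² = 181.5; / 0.9 = 201.7; / 2 = 100.8, i.e. about 101 per arm. No match.
- Equivalence by two one-sided 0.05 tests: 198 per level; / 0.9 = 220; / 2 = 110 per arm. No match.

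Of these variants only one-sided 5% non-inferiority with a 5-point margin gives 80.

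**2. Precision.** SE = 17 × √(2/144) = 2.00.

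**3. Power of the design rule.** One-sided 5%: Φ(5/2.003 − 1.645) = 0.80. One-sided 2.5%, i.e. the lower limit of a 95% CI: Φ(5/2.003 − 1.960) = 0.70.

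**4. Compare the two ways of reading the telephone coefficient (telephone minus usual).**

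- Two-sided 5% difference test: non-significant for any estimate within ±1.960 × 2.003 = ±3.9.
- Design rule, lower limit of the 90% CI above -5: the estimate must exceed -5 + 1.645 × 2.003 = -1.7.

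Estimates between about -3.9 and -1.7 are therefore non-significant and yet fail the hypothesis that the trial was sized for.

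**5. Operating characteristics.**

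| True difference | P(non-significant, but design rule not met) | P(design rule met) |
|---|---|---|
| 0 | 0.17 | 0.80 |
| -2.5 | 0.42 | 0.35 |
| -5 | 0.25 | 0.05 |

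At a true -5 the probability of a non-significant difference test is Φ((3.927 − 5)/2.003) = 0.30. At a true -6 it is Φ((3.927 − 6)/2.003) = 0.15.

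These figures ignore covariate adjustment, which could reduce the SE, and assume that the telephone effect does not depend on the EGP.

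**The case against.** The strongest reply is that the harmful rule is not in the text. The Statistical analyses section names a model. It gives no two-sided test or p-value threshold, and it does not say that non-significance will be taken as similarity. The telephone coefficient and its interval can be compared with -5 as they stand. Moreover, this is a journal article; a fuller protocol or SAP, not shown, may hold the decision rule. Nor does the article use the words non-inferiority or margin.

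Much of this stands. A reader might infer that the plan commits itself to reading a non-significant result as similar; it does not, and the 30% describes what a difference test would do if it were used that way. The regression needs no replacement. Non-inferiority is an inference, though the reproduced sample size supports it well. What remains is visible in the article itself: the stated purpose of the analysis does not match the hypothesis behind its sample size.

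Three stronger readings are also tempting.

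- **Intention-to-treat analysis dilutes the contrast**, because telephone patients who are not reassured get a clinic appointment. Under Nurse-led telephone follow-up, that appointment is part of the strategy itself, so it is not crossover. The documents give no crossover rate.
- **The claim should need agreement in a per-protocol set.** That is a trade-off, not a correction. A smaller set has less power, and the power of requiring both results cannot exceed it.
- **The Primary outcome measure section contradicts the sizing** when it says "The primary domain for improvement for both interventions in the trial is cancer-specific QoL". At least similar does not exclude better, and the article expects that fewer stressful visits could help QoL. The sentence names the outcome domain, not the test.

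**Conclusion.** The point holds as a mismatch between hypothesis and stated analysis. The telephone comparison was sized as one-sided 5% non-inferiority with a 5-point limit, and the analysis section describes a search for differences that is not linked to that limit. If the coefficient were judged by a two-sided 5% difference test, a true 5-point loss would go undetected about 30% of the time, where the sample size assumes a 5% error. The unstated side of the 0.05 level matters too: power is 80% at one-sided 5% and about 70% at one-sided 2.5%. That does not make the stated power wrong; it is correct at the level that reproduces 80 per arm.

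The size rests on SD 17, 10% dropout, equal allocation and pooling over the EGP. The documents do not support going further, to say that the regression is unsuitable, that intention to treat biases the result, or that the trial is too small for its own hypothesis.

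**What to change.** In Statistical analyses, add for the telephone factor:

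- At 12 months, telephone follow-up is concluded to be at least similar only if the lower limit of the two-sided 90% CI (one-sided 5%) for the adjusted mean difference, telephone minus usual, lies above -5.
- A non-significant difference is not evidence of similarity.
- The EGP comparison remains a superiority test.

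In Sample size calculations, state that the 80% power is at one-sided 5%, and that it would be about 70% at one-sided 2.5%.

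An analysis of patients followed as allocated may be added as a sensitivity analysis, not as a condition for the claim.

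The cost is analysis wording only: no new data, no more patients and no change of model. The rule should be fixed before outcome results are seen, because a limit or interval chosen afterwards would not be credible.

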### Randomisation

After written informed consent and completion of the baseline questionnaire, randomisation by minimisation is performed by the Comprehensive Cancer Centre Limburg. Patients are pre-stratified by treatment modalities and hospital. After randomisation, the research assistant contacts the patient and informs her about the assigned study-arm, thus whether she will receive standard or telephone follow-up and whether she will be invited to join the EGP.

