### Economic evaluation

Parallel to the trial an economic evaluation will be performed, comparing the costs and effects of each separate follow-up strategy, in order to determine the most cost-effective follow-up. The cost-effectiveness comparison thus includes four different strategies corresponding to the four study-arms. The cost-effectiveness ratio(s) will be expressed as the incremental cost per quality-adjusted life year (QALY). In order to be able to construct a QALY, the scores on the 5 dimensions of the EuroQol [29] are used. The cost-effectiveness analysis is performed from a societal perspective. Sensitivity analyses will subsequently be performed on several variables. For future costs and effectiveness data, a discount rate of 4% will be handled. In order to quantify the uncertainty surrounding the costs and effectiveness results, bootstrap analyses will be performed.

The cost-analysis from a societal perspective includes all health care costs and costs outside the health care sector. The cost-analysis will be performed by means of the micro-costing method, whereby a detailed inventory of the resource use per patient will take place [30]. Costs are calculated by multiplying resource utilisation with the cost-price per unit. Health care costs refer to hospital costs and costs of other health care facilities. Hospital costs consist of personnel, material, capacity costs and overhead associated with the four programmes and costs of (scheduled and unscheduled) outpatient hospital visits, telephone interviews and medical services (e.g. laboratory tests, bone scans, etc.). Most of these costs are estimated by using existing resource registration systems and available cost prices through the financial departments of the participating centres. In case true cost prices are not readily available in all participating centres the existing cost-prices of the University Hospital Maastricht or official directive prices are used [31]. Costs of telephone follow-up consist of personnel costs of the BCN and telephone costs. Costs associated with the EGP primarily consist of the personnel costs. Other health care costs include costs of visits to the general practitioner, medication, psychological and/or psychiatric (emergency) care.

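### The QoL regression does not name the baseline score as a covariate and is unclear on the two allocation factors; fitted as named it stays unbiased but gives up precision

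*Protocol article*

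**What the plan says.** Under Statistical analyses, QoL is compared by linear regression, run separately at 3, 6, 12 and 18 months. The EGP and telephone factors are both in the model, and "variables such as age, hospital treatment, and experienced support of a partner, will be brought into the model". Satisfaction, perceived control and anxiety are to be handled in the same way. The section mentions neither a change from baseline nor a repeated-measures model.

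Under Randomisation: "After written informed consent and completion of the baseline questionnaire, randomisation by minimisation is performed", and "Patients are pre-stratified by treatment modalities and hospital". A pre-randomisation QoL score is therefore available for each patient, and allocation depends on two named factors.

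Under Sample size calculations: "The primary outcome measure is cancer specific QoL at 12 months after randomisation". The planning values are "A baseline score of 64 with a standard deviation of 17", a threshold expressed as "we considered a change smaller than 5 points to be no change", and "with a power of 80% and a significance level of 0.05, the required number of patients per group is 80", with 10% dropout included.

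**The concern.** Two things are left loose in a model that is otherwise spelled out.

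- **Baseline score.** The baseline value of a QoL scale is usually one of the best predictors of its later value. Here it has no stated role in the treatment comparison, whether as covariate, change score or first measurement in a longitudinal model. The one use that the article spells out for the baseline questionnaires is comparing participants with non-participants. Without adjustment, intervals are wider than they need be, and a chance difference in baseline QoL between factor levels passes in part into the estimate.
- **Allocation factors.** Allocation is balanced on treatment modalities and hospital, but the model has one term, 'hospital treatment'. It could mean both factors with a comma lost, or one variable. If a factor that predicts outcome is balanced at allocation and then left out of the model, the model-based standard error is generally too large.

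The telephone comparison is where this matters most, because it asks whether QoL is at least similar within 5 points and its planned power has almost no slack.

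**Working it through.** **Inputs.** From Sample size calculations: SD 17, margin 5, power 80%, significance level 0.05 (sidedness not stated), 80 per arm, 10% dropout. The telephone comparison sets arms 2 and 4 against arms 1 and 3, so 160 per level are randomised and 160 × 0.9 = 144 are evaluable. Not in the article: the correlation r between baseline and 12-month QoL. I assume a range of 0.3 to 0.7.

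**Step 1: reproduce the stated size.** For non-inferiority with a true difference of zero at one-sided 0.05:

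n per level = 2 × [17 × (1.645 + 0.842) / 5]² = 142.9, so 143. Dividing by 0.9 gives 159 per level, 318 in total, or about 80 per arm. This matches the stated 320. One-sided 0.025 would need 406, so the article's figure corresponds to one-sided 0.05.

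**Step 2: power without baseline adjustment.** SE = 17 × √(2/144) = 2.00. Power = Φ(5/2.00 − 1.645) = 0.803. The EGP claim (10 points, two-sided 0.01) has power 0.992 with the same numbers. Both design claims therefore hold on the unadjusted SD.

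**Step 3: power with baseline QoL in the model.** The residual SD becomes 17 × √(1 − r²), and the SE shrinks by the same factor.

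| r (assumed) | SE | Power, one-sided 0.05 | 95% CI half-width (points) | Unadjusted / adjusted variance, 1/(1 − r²) | Total N for 80% power, with dropout |
|---|---|---|---|---|---|
| no adjustment | 2.00 | 0.803 | 3.93 | 1.00 | 318 |
| 0.3 | 1.91 | 0.834 | 3.75 | 1.10 | 292 |
| 0.4 | 1.84 | 0.860 | 3.60 | 1.19 | 270 |
| 0.5 | 1.73 | 0.892 | 3.40 | 1.33 | 240 |
| 0.6 | 1.60 | 0.930 | 3.14 | 1.56 | 206 |
| 0.7 | 1.43 | 0.968 | 2.80 | 1.96 | 164 |

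The comparator in the first row has no covariates at all. The planned model already carries age, 'hospital treatment' and partner support. Whatever outcome variance these share with baseline QoL is not a new gain, so the improvement over the actual plan is probably smaller than the table shows.

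**Step 4: size of a chance imbalance.** Neither allocation factor is QoL itself. If baseline QoL behaves as under simple randomisation, the SE of its difference between levels is 17 × √(2/160) = 1.90 points, and a gap of 2 points or more in either direction has probability of about 0.29. With r = 0.5 and equal SDs, a 2-point gap moves the unadjusted 12-month estimate by 0.5 × 2 = 1 point, a fifth of the margin. Over repeated randomisations this averages to zero; it is noise that adjustment would remove.

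**The case against.** The strongest reply is that this is a condensed article and its covariate list is illustrative. The words 'such as' neither include nor exclude baseline QoL, and a full covariate list is ordinary content for an analysis plan that is not shown. That is right as far as it goes: a reader might infer that the plan omits baseline QoL, and the text does not establish this. What remains is that the authors did specify a model and chose which covariates to name, and the most useful one is not named. An open list also leaves the decision on baseline adjustment until data are in hand.

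Other stronger readings also go beyond the text:

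- *A minimisation factor has been left out.* 'Hospital treatment' with a lost comma gives exactly the two allocation factors. The text supports ambiguity and no more. Even if a factor were missing, the usual consequence is a conservative standard error.
- *The trial is underpowered or the comparison biased.* Neither follows. The size was computed on the unadjusted SD and reproduces, and randomisation keeps both factor contrasts unbiased.
- *QALYs will be left unadjusted for baseline utility.* The Economic evaluation section says only "In order to be able to construct a QALY, the scores on the 5 dimensions of the EuroQol" are used. It is silent on adjustment, and silence in an article is no evidence of a defect.

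It is also fair to object that r is not in the documents. At r = 0.3 the power gain is only about 3 percentage points.

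**Conclusion.** The point stands as a low-cost improvement in efficiency and clarity. The named covariates give the pre-randomisation score no role and do not settle whether hospital and treatment modality are both in the model. If only those covariates were fitted, validity and the stated sample size would be untouched.

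The size of the loss depends on the assumed correlation. Over 0.3 to 0.7, baseline adjustment would lift power for the telephone comparison from 0.80 to between 0.83 and 0.97 (one-sided 0.05, margin 5, SD 17 at 12 months, 144 evaluable per level), and would narrow the 95% interval from ±3.93 to between ±3.75 and ±2.80 points. Read these gains as upper bounds relative to the planned model.

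**What to change.** Replace the open list by a closed one and state the model once:

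*Outcome at the time point = baseline value of the same scale + telephone + EGP + hospital + treatment modality + age + partner support as measured at baseline.*

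Use the same form for anxiety and perceived control. For a scale with no baseline measurement, as may be the case for satisfaction with follow-up, leave out the baseline term. Write hospital and treatment modality as two separate terms. Partner support is kept because the plan names it, but should be fixed at its baseline value: partners are invited to the EGP, so later answers could be affected by allocation.

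The cost is a change of wording. The baseline questionnaire and both allocation factors are already recorded before randomisation, and the sample size need not change.

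### The 12-month primary time point is not carried into the outcome definition or the four per-visit QoL regressions; one baseline-adjusted repeated-measures model with a 12-month primary contrast would settle it

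*Protocol article*

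**What the plan says.** Four places in the protocol article bear on the point.

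- **Sample size calculations.** Here the time point is explicit: "The primary outcome measure is cancer specific QoL at 12 months after randomisation, measured by the global health/QoL scale of the EORTC QLQ-C30". The planning values are "A baseline score of 64 with a standard deviation of 17". The margin for the telephone comparison is implied by "Consequently, we considered a change smaller than 5 points to be no change". On losses: "A dropout rate of 10% is accounted for in these calculations".
- **Abstract (Methods/design).** It names the global scale as primary endpoint, with no time point.
- **Primary outcome measure.** "The primary domain for improvement for both interventions in the trial is cancer-specific QoL". The instrument follows, again with no time point.
- **Statistical analyses.** For QoL, "the data will be analysed using a multivariate linear regression model", with both intervention factors in the model. Then: "The procedure will be performed 4 times as QoL is assessed at 3, 6, 12 and 18 months". Age, hospital treatment and partner support are given as examples of covariates; baseline QoL is not among them. Intention to treat is stated, and satisfaction, perceived control and anxiety are to be handled likewise.

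The Time schedule section describes contacting patients whose questionnaire is late. The article says nothing on how a missing questionnaire enters the analysis.

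**The concern.** The trial is sized on one visit, but the section that says how QoL will be tested lists four visits side by side and ranks none of them. A reader who has only the analysis section cannot tell which of the four results answers the primary question for either factor. That leaves the analyst a freedom that the sample size section did not intend.

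The second issue is the form of the model. A regression fitted at month 12 alone takes nothing from the same patient's month-3 and month-6 scores. If patients who are doing badly are more likely to be lost, the month-12 comparison is made on a favourable remainder. For the telephone question, where the aim is to show that QoL is at least similar, a loss of low scorers from the telephone arms pulls the estimate towards similarity. Adjusting for baseline QoL would give partial protection, but the article does not commit to it.

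**Working it through.** **1. The plan's own figure.** Inputs from the sample size section: SD 17, implied margin 5, power 80%, level 0.05, 10% dropout, and arms 2+4 against arms 1+3.

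n per factor level = 2 × 17² × (z_α + z_β)² / 5²

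- One-sided 0.05: 578 × (1.645 + 0.842)² / 25 = 143. Divided by 0.9 this is 159 per level, or 79.5 per arm. The stated 80 per arm is reproduced.
- One-sided 0.025: 182, or 203 after dropout, which is 101.5 per arm. This does not reproduce it.

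The plan's number therefore rests on a single comparison at one visit at one-sided 0.05. With 160 × 0.9 = 144 per level the power is 0.803. A sole 12-month primary contrast leaves the sample size as it stands.

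**2. Error rate if any of the four visits could count.** With four independent tests at 0.05: 1 − 0.95⁴ = 0.185. Visits on the same patients are correlated. The article gives no correlation, so 0.5 to 0.7 is assumed. Simulating four equally correlated standard normal statistics (2,000,000 draws) gives the chance of at least one false positive for one factor:

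| Assumed correlation | two-sided 0.05 | one-sided 0.05 | two-sided 0.01 |
|---|---|---|---|
| 0.5 | 0.156 | 0.144 | 0.035 |
| 0.6 | 0.144 | 0.132 | 0.033 |
| 0.7 | 0.131 | 0.120 | 0.030 |

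The one-sided column fits the telephone comparison as sized. The 0.01 column fits the level at which the group programme was powered. The analysis section states no test level, so all three are shown. With month 12 alone as primary, each entry falls back to its nominal level.

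**3. Possible shift from losses at month 12.** This part is illustrative; every dropout input is an assumption. Settings:

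- true telephone difference −5 at every follow-up visit, SD 17, between-visit correlation 0.5 or 0.6;
- 8% loss at random in usual care;
- 10 to 14% loss in the telephone arms, with the log-odds of loss rising by 0.5 to 1.2 for each SD by which the 6-month score is lower.

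Expected month-12 difference among patients with a month-12 score:

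- unadjusted: −4.6 to −3.6, a shift of 0.4 to 1.4 points;
- adjusted for baseline QoL: −4.8 to −4.4, a shift of 0.2 to 0.6 points;
- likelihood-type estimate using the earlier scores: −5.0.

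The last result follows from the set-up, because loss was generated from the observed 6-month score. It shows what a repeated-measures model can recover when data are missing at random, and no more than that.

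**The case against.** The strongest reply is that the primary time point is fixed. The sample size section states it without qualification, and no other section contradicts it. Fitting the model at each visit is compatible with one primary and three supportive analyses. This stands, and it makes the multiplicity conditional.

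A reader might infer that the plan allows success at any visit. It does not say so; it only fails to say the opposite. A reader might also count eight tests and combine both factors into an error rate of about 0.24 to 0.29, from 1 − (1 − 0.13)² to 1 − (1 − 0.156)². That figure is not supported. It merges two separate factorial questions, treats the telephone comparison as a two-sided test of difference although it is framed as at least similar, and applies 0.05 to the group programme, which was powered at below 0.01.

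A further tempting reading is that only returned questionnaires are analysed and that partly observed patients are dropped despite intention to treat. The article says neither. Per-visit regressions do not rule out imputation, and missing-data handling is commonly left to the full protocol or the analysis plan. A patient without month 12 would still enter the regressions for the other visits attended. The covariate list is illustrative, so baseline QoL is not excluded either. What remains is narrower: the model that the article does prescribe borrows nothing across visits unless something is added to it.

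Finally, a regression at a prespecified 12-month visit is a valid primary analysis. The mixed model is an improvement, not the repair of an invalid method.

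**Conclusion.** The point holds in limited form. The 12-month primary appears in the sample size section only, and the prescribed analysis is four unranked regressions that do not name baseline QoL.

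If the sample size section is honoured, there is no inflation from the time points. If it is not, the per-factor error rate is roughly three times nominal: 0.13 to 0.16 at two-sided 0.05, 0.12 to 0.14 at one-sided 0.05, and about 0.03 at 0.01. All of these depend on the assumed correlations of 0.5 to 0.7.

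The possible bias ranges from some tenths of a point with baseline adjustment to more than 1 point without it, towards no difference, against a margin of 5. It rests wholly on an assumed pattern of loss that nothing in the article suggests, and on there being no imputation. It should be read as a reason to prefer the better model, not as evidence that this trial's estimate will be biased. The 10% allowance in the sample size covers the power at that rate of loss; it does not address bias.

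**What to change.** In the primary outcome and statistical analysis sections, state that the 12-month contrast in global QoL is the sole primary test for each factor, and that 3, 6 and 18 months are secondary.

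Replace the four regressions by one linear mixed model for repeated measures with baseline QoL, time, each factor by time and an unstructured covariance matrix. Take the primary contrasts at month 12 from it, and report the other visits as secondary estimates from the same model.

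The cost is a change of wording, slightly more modelling work, and reliance on a missing-at-random assumption, which should be stated. No new data are needed, and 80 per arm is unchanged.
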